**Methods/Design:**

The Bath Breakfast Project (BBP) is a randomised controlled trial comparing the effects of daily breakfast consumption relative to extended fasting on energy balance and human health. Approximately 70 men and women will undergo extensive laboratory-based assessments of their acute metabolic responses under fasted and post-prandial conditions, to include: resting metabolic rate, substrate oxidation, dietary-induced thermogenesis and systemic concentrations of key metabolites/hormones. Physiological and psychological indices of appetite will also be monitored both over the first few hours of the day (i.e. whether fed or fasted) and also following a standardised test lunch used to assess voluntary energy intake under controlled conditions. Baseline measurements of participants' anthropometric characteristics (e.g. DEXA) will be recorded prior to intervention, along with an oral glucose tolerance test and acquisition of adipose tissue samples to determine expression of key genes and estimates of tissue-specific insulin action. Participants will then be randomly assigned either to a group prescribed an energy intake of ≥3000 kJ before 1100 each day or a group to extend their overnight fast by abstaining from ingestion of energy-providing nutrients until 1200 each day, with all laboratory-based measurements followed-up 6 weeks later. Free-living assessments of energy intake (via direct weighed food diaries) and energy expenditure (via combined heart-rate/accelerometry) will be made during the first and last week of intervention, with continuous glucose monitors worn both to document chronic glycaemic responses to the intervention and to verify compliance.

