### Experimental Protocol

***Objective i - ***The first phase of the proposed work (Phase I) will involve two laboratory-based examinations of the acute metabolic and behavioural responses to extended fasting relative to ingestion of a standardised breakfast. These trials will be applied in a randomised and counterbalanced order with 3-28 days interval except for eumenorrheic women, whose trials will be separated by 28 ± 2 days and only at least 3 and at most 10 days after the onset of menses (i.e. follicular phase) to ensure that the effects of menstrual cycle on the majority of hormones and therefore resting metabolic rate (RMR) and appetite will be both minimal and standardised between trials [69-71]. These acute trials will be conducted in our resting metabolism laboratory in accordance with current guidelines for best practice in measuring resting metabolic rate [72]. Most notably, ambient temperature in this laboratory is maintained between 20 and 25°C (with intra-individual trials standardised within 2°C) and participants will arrive for testing at 8 am (±1 h) in a 10 hour fasted state but having ingested 1 pint of plain water upon waking following standardised physical activity and diet (the latter to incorporate either daily breakfast or extended fasting according to the group randomisation described later, thus permitting meaningful comparisons with follow-up visits). Repeated 5 minute resting expired gas samples will be collected over 30 minutes (after 20 minutes of quiet rest) to establish RMR and substrate selection before a cannula will be fitted to an antecubital vein for the acquisition of a baseline 15 ml blood sample, along with further samples throughout that day.

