
The bowl of pasta will be refilled every 10 minutes to minimise any visual feedback in the regulation of appetite. To gain additional insight regarding psychological reward and food hedonics, a validated labelled magnitude scale [76] will be administered following the first and last mouthful of this meal to reliably assess the degree of 'pleasantness' associated with ingestive behaviour. The 3 hour post-prandial period will then be repeated exactly as following breakfast (but without the 15-30 minute samples) to track metabolic responses to lunch.

***Objective ii - ***Phase II of testing will commence within 3-28 days after completion of each participants' second trial under Phase I of testing (thus using participants' breakfast trial along with the measures described above as a baseline). This trial schedule will again be used for all participants other than for eumenorrheic women, who will follow the same restrictions as described above and therefore occasionally be required to complete their first trial under Phase II prior to the completing the second trial under Phase I. In such cases, these participants' 6-week intervention will simply be deferred for two weeks (i.e. enabling completion of Phase I) to allow follow-up measures to be taken at the same stage in the menstrual cycle. The first visit under Phase II will begin with participants again arriving in the laboratory at 8 am (±1 h) having adhered to the same standardisation procedures as described for Phase I. Measurements of body mass and adiposity based on hip and waist circumference (i.e. widest gluteal girth & mid-point between lowest rib and iliac crest, respectively), sagittal abdominal height (using a Holtain-Kahn calliper at the iliac crest) and body composition via DEXA (Hologic Discovery W) will also be made at this visit, before a small (~1 g) sample of subcutaneous adipose tissue will be acquired using a 14 G needle to determine basal expression of key genes related to appetite and physical activity regulation (e.g. adiponectin and leptin) and energy expenditure (e.g. UCPs).

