This second phase of data collection will involve each participant being randomly assigned either to an extended daily fasting group (only plain water permitted until 1200 each day) or a breakfast consumption group (prescribed intake of ≥3000 kJ before 1100 each day, to include at least 1500 kJ within two hours of waking) for a period of 6 weeks [a duration previously shown to be sufficient for dietary modification to induce detectable changes in energy balance and body composition; [35]. To facilitate this process, participants assigned to the breakfast group will be provided with detailed examples of appropriately energetic breakfasts and the energy content of other typical breakfast foods, although the breakfasts consumed will ultimately be self-selected by each individual on a daily basis. Upon completion of this 6 week dietary modification, participants will return to the laboratory for follow-up of all anthropometric measures and a second subcutaneous adipose tissue biopsy to determine whether the intervention has altered the expression of those genes measured at baseline (described above).

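### For eumenorrheic women in the usual visit order, the 6-week follow-up conflicts with the protocol's own day 3-10 cycle window, and the two-week deferral that addresses this is written only for the reversed order

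*Protocol article*

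**What the plan says.** All of the following is in the Protocol article.

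- **The window.** Experimental Protocol, Objective i, sets two limits for eumenorrheic participants. On spacing, they are a group "whose trials will be separated by 28 ± 2 days". On cycle day, their visits may take place "only at least 3 and at most 10 days after the onset of menses". The stated reason is to keep cycle effects on most hormones, and hence on resting metabolic rate and appetite, small and equal between trials.
- **Its reach.** Under Objective ii these are women "who will follow the same restrictions as described above and therefore occasionally be required to complete their first trial under Phase II", before they finish Phase I. The window is therefore a Phase II rule too, and the reversed order is described as an occasional event.
- **The interval.** The Abstract (Methods/Design) has participants randomised "with all laboratory-based measurements followed-up 6 weeks later". Objective ii agrees: "Upon completion of this 6 week dietary modification, participants will return to the laboratory for follow-up of all anthropometric measures".
- **The exception.** For the reversed order only: "In such cases, these participants' 6-week intervention will simply be deferred for two weeks". The text explains that this lets Phase I be completed, and gives the purpose as "to allow follow-up measures to be taken at the same stage in the menstrual cycle".
- **The final breakfast trial.** It comes at least 2 days after the Phase II follow-up. Up to 7 days are allowed only where the cycle need not be controlled or where both trials still fall in the follicular phase.

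**The concern.** Six weeks is one and a half cycles of 28 days, so a visit early in one cycle is followed by a visit well past the early part of another. The two-week deferral shows that the authors saw this and meant follow-up to match baseline. As worded, the deferral reaches only the occasional reversed-order woman. A woman in the usual order has already completed Phase I, so the explanation attached to the deferral does not cover her, yet she faces the same calendar problem.

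At stake are the baseline-to-follow-up changes measured in the laboratory in these women. Two visits carry them. The Phase II visits hold anthropometry, DEXA, the adipose sample and the glucose tolerance test. The repeated breakfast trial holds resting metabolic rate, appetite, hormones and lunch intake, which include the quantities the window was written to protect. Women in the two visit orders would also be handled differently for no stated reason.

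**Working it through.** **Inputs**

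- Permitted baseline days: d = 3 to 10, eight values (Experimental Protocol, Objective i).
- Interval from first Phase II visit to follow-up: G = 42 days (6 weeks), taking the intervention to start soon after that visit. The gap is not stated; the 6-weeks-later wording in the Abstract implies that it is short.
- Deferral: 14 days (Objective ii).
- Final breakfast trial: at least 2 days after the Phase II follow-up, so G = 44 or more.
- Cycle length L: not stated. 28 days is assumed, in line with the 28 ± 2 day spacing; 21 to 37 days were examined.

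**Formula.** Cycle day at follow-up = d + G − kL, for the whole number k that puts the result in 1 to L. Follow-up is in the window if the result lies in 3 to 10.

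**1. The plan's own remedy.** With deferral, G = 14 + 42 = 56 = 2 × 28. At L = 28, d + 56 − 56 = d, so all 8 baseline days return to the same cycle day. The deferral does what the plan says it does.

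**2. Usual order, no deferral, G = 42**

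| L (days) | Follow-up day for d = 3 to 10 | In window |
|---|---|---|
| 26 | d + 16: 19-26 | 0 of 8 |
| 28 | d + 14: 17-24 | 0 of 8 |
| 30 | d + 12: 15-22 | 0 of 8 |
| 34 | d + 8: 11-18 | 0 of 8 |
| 35 | d + 7: 10-17 | 1 of 8 |
| 37 | d + 5: 8-15 | 3 of 8 |

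The count is 0 of 8 for every L from 25 to 34. At L = 25, d + 42 − 50 = d − 8 is at most day 2. Some baseline days succeed below 25 (at L = 24, d − 6 gives days 3 and 4 for d = 9 and 10; at L = 21, 42 = 2 × 21 and all eight succeed) and from 35 upwards.

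**3. Spacing rule.** 42 is not in 26-30, nor in the two-interval multiple 52-60. 56 is in the latter.

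**4. Final breakfast trial.** At the 2-day minimum, G = 44. At L = 28, d + 44 − 28 = d + 16, which gives days 19-26: 0 of 8.

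**5. How much unstated gap would be needed.** The latest baseline day, d = 10, is the first to re-enter the window, at day 3. The extra delay needed is 2L + 3 − 52 days: 3 at L = 26, 7 at L = 28 and 11 at L = 30. All eight days return at L = 28 only with 14 extra days, which is the deferral itself.

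**6. Limit of a fixed 56 days.** At L = 27 or 29, 6 of 8 baseline days stay in the window; at L = 26 or 30, 4 of 8.

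**The case against.** The strongest reply is that this is a loose sentence, not a plan to measure out of phase. The article says that these women keep the same restrictions in Phase II, states the aim of the deferral, and again assumes follicular-phase trials when it limits the delay before the last visit. Staff who follow the governing rule would schedule accordingly. The start gap is not given, and visit calendars often sit in a full protocol. It is true that the intent is clear and that the calculation depends on a short gap. But the article does not merely leave detail out: it states a window, an interval and an exception, and together these do not fit the usual order. Reading the exception as covering all eumenorrheic women would resolve the conflict, but the explanation about completing Phase I points the other way, and the wording would still need correcting.

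A second reply is that resting metabolic rate, appetite and hormones have the Phase I breakfast trial as their baseline, so the 42-day interval is not theirs. That is correct, but the final breakfast trial follows the Phase II follow-up, and step 4 puts it outside the window at 28 days.

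A reader might also infer more than the documents support:

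- *That the trial's comparison is biased.* Objectives ii and iii compare two randomised groups on the same visit schedule, so a phase shift is not expected to differ systematically by arm.
- *That every follow-up is luteal, or that the window can never be met.* Neither holds at all cycle lengths; at 34 days follow-up falls on days 11-18.
- *That most participants are affected.* The point concerns eumenorrheic women only. That most of them follow the usual order is inferred from the reversed order being called occasional.
- *That body mass is among the variation the window was meant to remove.* The stated rationale names hormones, resting metabolic rate and appetite.

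**Conclusion.** The conflict is real and confined to eumenorrheic women in the usual visit order. Given an intervention that starts soon after the first Phase II visit and regular cycles of 25-34 days, a 6-week follow-up misses the day 3-10 window from every permitted baseline day; at 28 days it falls on days 17-24.

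The effect is extra noise in these women's laboratory outcomes, within-arm change mixed with cycle phase, and unequal handling of the two visit orders. The number of women is not stated, so the size of the effect on any outcome cannot be given. Free-living energy expenditure, the quantity behind the sample size, is recorded in the first and last weeks of the intervention, not at these visits, and is not affected. This should be corrected, but it does not threaten the main randomised comparison.

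**What to change.** Reconcile the Abstract (Methods/Design) with the Objective i and Objective ii text of Experimental Protocol, including the paragraph on the final breakfast trial. The baseline-to-follow-up interval should meet the document's own window for every eumenorrheic woman to whom it applies, whatever the visit order, and the gap between the first Phase II visit and the start of the intervention should be stated. How this is done is for the investigators. They should note that a fixed 56 days meets the window from all baseline days only near a 28-day cycle (step 6).

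Inclusion Criteria already require women to keep a record of cycle phase or contraceptive use. Use it to flag any follow-up outside the window, and report a sensitivity analysis of the laboratory outcomes with an in-window/out-of-window term.

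The cost is a clarification of the text, about two weeks more calendar time for some women if the plan's existing deferral is the route chosen, and some loss of precision in the sensitivity analysis. Dropping out-of-window pairs altogether would not be free either: if the present wording were followed, it could remove most eumenorrheic women.

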At this stage, participants will provide ratings of hunger and appetite using validated visual analogue scales [73], for subsequent follow-up post-breakfast and also pre-post lunch and at the end of day. They will then receive either no breakfast or a typical standardised breakfast (composed of cereal, toast and orange juice) with the opposite treatment applied in each participant's second trial). The specific food and macronutrient composition of this breakfast has been described previously [74] and provides quantities intended to deliver 14 mg carbohydrate per kJ of each individual's previously established RMR. Fifteen minutes later or upon completion of the breakfast (if longer than 15 minutes is required) a 3 hour post-prandial period will commence, involving collection of all urine output (for determination of urea nitrogen excretion) with hourly expired 5 minute gas samples to assess changes in substrate metabolism (i.e. carbohydrate, lipid and protein oxidation) and DIT (i.e. post-prandial energy expenditure minus RMR). Fifteen millilitre blood samples (including 5 ml waste) will also be drawn 15, 30 & 60 minutes post-breakfast, then at hourly intervals to determine systemic concentrations of: glucose; lactate; insulin; NEFA; urea; 'energy balance hormones' that are known to play a central role in the regulation of metabolic rate, appetite and spontaneous physical activity (e.g. free thyroxine, adiponectin, CCK, total/acylated ghrelin, leptin & PYY); and also cytokine concentrations (e.g. interleukin-6 and TNF-α), in view of recently documented differences in post-prandial inflammatory responses to varied meals across different populations [75] (with low/high density lipoprotein cholesterol and CRP only followed-up at the 3 hour time-point). Participants will then be provided with a test meal of standardised composition (1 kg cooked Sainsbury's™ penne pasta and Ragu™ traditional tomato sauce; prepared at a ratio of 1:1 uncooked mass) along with *ad libitum *plain water (although participants will ingest the same volume of water as in their first trial during all subsequent visits), which we have previously employed during pilot work to estimate likely differences in voluntary energy intake. At this stage, participants will be left alone in the laboratory and receive a recorded message stating: "We ask that you continue eating until you have satisfied your hunger. The lunch will remain in front of your for at least 30 minutes, at which point the post-lunch timer will be started, although you will be allowed to continue eating if you are still hungry."

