
After each participant's follow-up trial under Phase II, participants will continue adhering to their assigned intervention for at least 2 days to allow for the 48 hour dietary control (although up to 7 days will be permitted in participants for whom either the menstrual cycle need not be controlled for or when both trials can still occur within the follicular phase) before returning to the laboratory to repeat their breakfast trial exactly as described in relation to Objective i. This trial will therefore inform whether acute metabolic and/or behavioural effects may be modified following chronic exposure to each treatment. A formal exit interview will also be incorporated into this final visit during the afternoon post-prandial period to obtain qualitative data regarding participants' experiences of the study and motives for any perceived changes in behaviour.

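### The exit interview sits inside the measured post-lunch period of the final visit only, so that visit is not the exact repeat of the baseline breakfast trial that the plan calls for

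*Protocol article*

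**What the plan says.** All of this is in the Protocol article, Experimental Protocol.

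- **Final visit (Objective ii).** After the six-week intervention and a short further period of adherence, participants continue "before returning to the laboratory to repeat their breakfast trial exactly as described in relation to Objective i". The stated purpose is to learn whether acute metabolic or behavioural effects change after chronic exposure.
- **Baseline.** Phase II takes the Phase I trial as its reference: "thus using participants' breakfast trial along with the measures described above as a baseline".
- **Afternoon of each such trial (Objective i).** "The 3 hour post-prandial period will then be repeated exactly as following breakfast (but without the 15-30 minute samples) to track metabolic responses to lunch".
- **What the post-breakfast period contains.** All urine is collected. There are "hourly expired 5 minute gas samples to assess changes in substrate metabolism" and diet-induced thermogenesis, and "blood samples (including 5 ml waste) will also be drawn 15, 30 & 60 minutes post-breakfast, then at hourly intervals". Appetite is rated at the start, "for subsequent follow-up post-breakfast and also pre-post lunch and at the end of day".
- **Interview (Objective ii).** "A formal exit interview will also be incorporated into this final visit during the afternoon post-prandial period". It asks about experiences of the study and the reasons for any change in behaviour that participants perceive.

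**The concern.** The final visit is described as an exact repeat of the baseline trial, yet it contains a procedure that the baseline trial lacks, in a period when data are being collected. A conversation about how the study went and why habits changed is not obviously neutral for resting gas exchange, or for an appetite rating given later that day.

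What is at stake is the before-after reading of the afternoon data: post-lunch energy expenditure and substrate oxidation, post-lunch metabolites, hormones and cytokines, and the last appetite rating. If any of these differ between baseline and follow-up within a person, adaptation to the intervention cannot be separated from the effect of being interviewed.

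The placement also sits oddly with the care taken elsewhere. The plan standardises room temperature within a person, fixes the volume of water drunk across visits, leaves participants alone with the test lunch and gives the lunch instruction by recording.

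**Working it through.** No figure in the plan bears directly on this point, so the check is a comparison of the two visits.

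**1. Is the afternoon measured?** Yes. The post-lunch period copies the post-breakfast period apart from the two early samples. That leaves, over 3 h (180 min):
- gas: one 5 min collection each hour, 3 × 5 = 15 min in total;
- blood: at 60 min and then hourly, so at 60, 120 and 180 min;
- urine: collected throughout;
- appetite: a rating at the end of the day, which reads as closing the visit.

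**2. Is the interview in that window?** Yes. The text places it in the afternoon post-prandial period.

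**3. Is it matched at baseline?** No. The account of the Phase I trials describes no interview or equivalent activity.

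**4. Must it overlap a measurement?** Not necessarily. Gas collection takes 15/180 = 8.3% of the window, so the interview could be fitted between collections. The article does not require this. Spacing the interview around the gas collections would not by itself protect the later blood samples or the end-of-day rating.

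**5. Which results are exposed?**

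| Measure | Relation to the interview |
|---|---|
| Fasting resting metabolic rate | Before it |
| Post-breakfast gas, blood, appetite | Before it |
| Test-lunch intake, pleasantness ratings, pre- and post-lunch appetite | Before the afternoon period |
| Post-lunch gas, blood, urine | Same period |
| End-of-day appetite | After it |
| DEXA, biopsy, glucose tolerance test, free-living intake, expenditure and glucose | Other occasions |

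**6. Which comparison is exposed?** Let d be the shift that the interview produces at follow-up.
- Within a person, observed change = true change + d.
- Between arms, difference in change = true difference + (d in the fasting arm − d in the breakfast arm). If d is the same in both arms, it cancels.

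The within-person contrast is in use. The repeat trial is there to show modification of acute responses, the Statistical Approach section provides for paired tests between trials, and the text on Objective iii contrasts cytokine responses, C-reactive protein and lipids between the baseline and final trials.

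**7. Is the sample size affected?** No. It rests on daily energy expenditure (difference 2700 kJ/d, SD about 2000 kJ/d, two-sided 0.05, 90% power). A two-sample t-test needs 12.6, so 13 per group, against the plan's figure of about 14. Recruitment is 60/0.86 = 69.8, so 70. Neither figure involves the afternoon data.

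**The case against.** The best defence has four parts.

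- **Randomisation protects the main comparison.** Objectives ii and iii are a parallel-group contrast, and both arms have the same interview at the same visit. This largely stands. A reader might infer that the shift fails to cancel because one arm talks about fasting and the other about eating breakfast. That is conceivable, but nothing in the document shows that interview length or content differs by arm, or that such a difference would alter gas exchange, hormones or appetite.
- **Overlap with a sample is not shown.** This stands as far as it goes. The text does not say that the interview coincides with any collection, and minute-by-minute scheduling is the sort of detail an article leaves to the full protocol. The article does, however, fix the period, and it is a measured one.
- **The baseline condition is not itself described as silent.** Quiet rest is specified only for the 20 minutes before resting metabolic rate is measured. This also stands: what participants did between hourly samples at baseline is not stated. It weakens any claim that baseline was neutral, but a formal interview is still an addition at one visit only.
- **Using waiting time limits burden.** The day already starts at about 8 am and includes two 3 h periods and a lunch of at least 30 minutes, in a trial that worries about drop-out. This is a fair reason for the placement and is the real cost of changing it.

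A reader might also see a fault in the interview reaching only those who attend the final visit. The plan already documents losses to follow-up and compares data from those lost with data from completers. Interviewing people who withdraw would be an optional extra, and its absence is not an error.

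**Conclusion.** The point holds as a minor internal inconsistency. The final visit is declared an exact repeat of the baseline trial, but it carries a formal interview, in a measured period, that the baseline trial does not describe. The within-person change in post-lunch gas, blood and urine measures and in end-of-day appetite, all secondary, is therefore collected under unmatched conditions. The between-arm comparison of change is largely protected, on the assumption that the interview acts alike in both arms.

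The size of the disturbance cannot be derived from the document. It would be tempting to assume some percentage rise in energy expenditure during the interview and set it against the roughly 150 kJ metabolic effect of breakfast in the power section. The document does not support that. It gives no such percentage, and the 150 kJ is a pre-lunch difference between breakfast and continued fasting, whereas the exposed quantity is a post-lunch change between two days on which breakfast was eaten.

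**What to change.** Change the sentence on the exit interview so that it takes place after the last post-lunch gas, blood and appetite measurement of the final visit. The repeat trial then matches Phase I as the plan says it should, and no analysis has to change.

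The cost is one sentence in the visit schedule and a final day that is longer by the length of the interview, which the article does not state. Keeping the interview in the period but clear of the gas collections would be a weaker remedy, because later blood samples and the end-of-day rating would still follow it.
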